### Participant timeline {13}

The participant timeline is exhibited in Fig. 1.

**Fig. 1 Fig1:**
[figure not shown]
Participant timeline. Asterisk symbol (*) indicates the following: if hospital discharge occurs first, intervention is stopped at discharge. Superscript digit one (1) indicates the following: demographics, clinical status according to nine-level ordinal scale, medical history, smoking status, COVID-19 symptoms, and COVID-19 vaccination status. Superscript digit two (2) indicates the following: C-reactive protein, neutrophil-lymphocyte ratio, interleukin-6, and procalcitonin. Superscript digit three (3) indicates the following: on a visual analog scale from 0 to 10. Superscript digit four (4) indicates the following: Clinical status on nine-level ordinal scale, admission to ICU, ventilation, mortality, complications. MRC, Medical Research Council dyspnea scale; SF-12v2, 12-item Short Form Survey version 2

### Sample size {14}

Based on the effect of aviptadil in previous trials described in the introductory section, we assume that patients in the experimental group will show a 1.75-fold hazard to have a clinical improvement as compared to patients in the control group (hazard ratio (HR) = 1.75) [42, 50]. Furthermore, based on previously published results for current standard care, we assume an overall probability of 80% for reaching the primary endpoint (clinical improvement) within 28 days (*d* = 0.8) [56, 57]. Group allocation shall be divided equally ($$\frac{1}{2}n={n}_1={n}_2$$).

Testing for two-sided equality in a Cox proportional hazards model at a significance level of *α* = 0.05 and aimed power of 80% (*β* = 0.2), we are applying the sample-size formula in Chow as follows [58]:$$n=\frac{{\left({z}_{\alpha /2}+{z}_{\beta}\right)}^2}{b^2\ast 0.25\ast d}=\frac{{\left(1.96+0.84\right)}^2}{{\mathit{\log}}^2(1.75)\ast 0.25\ast 0.8}\approx 125.2$$where *b* =  *log* (*HR*) =  *log* (1.75).

Estimating a drop-out rate of 3% and considering block randomization, we aim to include 132 patients into the study.

### Recruitment {15}

All hospitalized patients at a study center who fulfill the eligibility criteria are asked to take part in this study. In order to reach the target sample size within the planned time frame, the study is geographically expanded to several centers within Europe.

### Assignment of interventions: allocation

#### Sequence generation {16a}

The group-allocating randomization code is a computer-generated sequence, using block randomization with block size of four. Each block determines assignment of four patients to the two groups, while two patients are assigned to the intervention group and two patients are assigned to the control group in a random order. Randomization is stratified by study center in order to account for differences in standard of care. Block randomization also accounts for differences in standard of care according to time elapsed since the start of the pandemic.

#### Concealment mechanism {16b}

The entire concealment process is handled in the pharmacy that produces the study drug. Identically looking vials with doses of either 3 ml aviptadil solution (67 μg/ml, experimental group) or 3 ml NaCl 0.9% (placebo group) are filled in the pharmacy in a 1:1 ratio. Kits of 10 vials of the same content (one vial per treatment day, for a maximum of 10 days) are then packed and labeled with a continuous kit number. The actual content of each kit (aviptadil or placebo) is determined by the randomization sequence described above, while the kit number represents the concealed randomization code. For each kit, the description of the actual content (aviptadil or placebo) is packed in a separate concealed envelope, with only the kit number visible from the outside. The respectively allocated kits and concealed envelopes are shipped to the coordinating study center in Liestal. From here, they are distributed to each study center and used in the order of the kit number indicated on the label. Upon inclusion of a patient, the allocated kit number is documented in the CRF. The concealed envelopes containing the description of group allocation are stored at the coordinating study center in Liestal.

#### Implementation {16c}

The entire concealment process is handled in the pharmacy that produces the study drug. Study physicians at the respective study center will enroll participants into the study and hand out the kits containing the study drug in the order of the assigned kit numbers. Group assignment is pre-defined by order of the kit numbers and the content of the respective kit.

### Assignment of interventions: blinding

#### Who will be blinded {17a}

Trial participants, investigators, treating physicians, study personnel administering the inhalation, and data analysts are blinded to group allocation. Since the study drug is filled into identically looking vials and aviptadil solution and placebo are not visually distinguishable, blinding is ensured until unblinding procedures are actively undertaken.

#### Procedure for unblinding if needed {17b}

If a treating physician of a participating patient needs to know for medical reasons (i.e., AE, SAE), if the patient is assigned to the interventional or control group, he/she can call a 24-h phone hotline to receive information about the patient’s group allocation. Unblinding is undertaken by a trained study team member, who opens only the envelope with the respective kit number.

### Data collection and management

#### Plans for assessment and collection of outcomes {18a}

All required patient data at baseline, during hospitalization, at discharge and follow-up are recorded on paper-based case report forms (CRFs). Trained study personnel at each site transfer the data into a web-based electronic case report form. A copy of the CRF used in the trial is available on reasonable request. Laboratory analyses comprise only standard parameters and are performed in the accredited in-hospital laboratories at each site. Patient dyspnea is assessed at inclusion and follow-up by means of the Medical Research Council dyspnea scale (MRC), which has been studied in a variety of respiratory conditions, including COVID-19. Patient-reported outcome is assessed at follow-up by means of the instrument SF-12v2, which is a validated survey for investigating health-related quality of life in a variety of both acute and chronic conditions, including lung diseases.

#### Plans to promote participant retention and complete follow-up {18b}

Patients participating in the study do not receive financial reimbursement. Expenses for the study medication and diagnostics performed only during this study are covered by the study budget. The 28-day follow-up is a phone call, initiated by a study team member at the respective study center. In case of withdrawal of consent or premature termination of the study, data and samples are evaluated in encrypted form until termination of the study.

#### Data management {19}

Data acquisition and entry into the web-based and password-protected electronic data capture system (SecuTrial®) are performed by trained staff at the participating study centers. Personal contact information, which is needed for follow-up phone calls, is stored separately and only accessible for the staff members executing these phone calls. Any paper documents, such as informed consent forms, are stored in locked cabinets in restricted access areas at the respective participating study centers. Electronic records are stored on a password-protected server. All records are archived for a minimum of 10 years after study termination or premature termination of the clinical trial at the respective participating study center. A data management plan documents details for the data processing and is available from the authors upon reasonable request.

#### Confidentiality {27}

All collected patient data are treated as confidential and stored and analyzed in a coded way in accordance with data protection principles. Results will be published in anonymized fashion. Direct access to source documents is permitted for purposes of monitoring, audits, and inspections. The study data and protocol shall be accessible to regulatory authorities for at least ten years after study termination.

#### Plans for collection, laboratory evaluation, and storage of biological specimens for genetic or molecular analysis in this trial/future use {33}

The trial does not involve collecting biological specimens for genetic or molecular analysis.

## Statistical methods

### Statistical methods for primary and secondary outcomes {20a}

R will be used for all statistical analyses [59]. Primary and secondary endpoints will be summarized by group using descriptive statistics (mean ± standard deviation for normally distributed data, median and interquartile range for other continuous data, absolute and relative frequencies for categorical data). A log-rank test will be used to compare Kaplan-Meier curves for the primary endpoint “time to clinical improvement,” with failure to reach clinical improvement or death before day 28 being right-censored at day 28. Sensitivity analyses will be performed with “death” and “clinical improvement” as competing risks. For potential confounders that are not fully balanced by randomization, adjusted analyses for the primary outcome may be performed using Cox regression models to estimate hazard ratios with corresponding two-sided 95% confidence intervals to compare with the respective unadjusted Cox model. The proportionality assumption for the Cox proportional hazards models will be tested by assessing Schoenfeld residuals.

Treatment effects on binary secondary endpoints will be analyzed by means of chi-squared test, or Fisher’s exact test, in case expected sub-group size is smaller than five. For discrete secondary endpoints, group differences will be assessed using a Poisson or negative binomial regression, depending on the underlying distribution. Treatment effects on patient-reported severity of symptoms will be analyzed with an ordinal logistic regression and an additional longitudinal analysis with cumulative link mixed models. Effects on longitudinal changes in infection-related biomarkers will be assessed using mixed effect linear regression and analysis of covariance. Patient-reported impact on health at day 28 will be compared between the two groups by means of Student’s *T*-test, or Mann-Whitney-*U* test, depending on normality of the data.

All statistical tests will be performed using two-sided tests at the significance level 0.05. Detailed methodology for statistical analyses of the data collected in this trial is documented in a separate statistical analysis plan (SAP). The SAP is finalized before database closure and can be obtained from the authors upon reasonable request. A summary of the SAP is provided in Additional file 1.

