### Trial design {8}

This study is a multicenter, placebo-controlled, double-blinded, randomized phase II trial with 132 adult patients. In a parallel group design, patients will be randomly allocated in a 1:1 ratio to inhale either aviptadil (67 μg three times a day) or normal saline (1 ml three times a day) for 10 days, or until hospital discharge, in addition to standard care. The study is conducted as a superiority trial.

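### Allocation is stratified by centre because care differs between centres, but the primary log-rank test is stated without strata; if centres do differ, the test is conservative and loses power.

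*Protocol article*

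**What the plan says.** Under Sequence generation {16a}, the protocol article uses blocks of four within each centre: "Randomization is stratified by study center in order to account for differences in standard of care". The abstract repeats the stratification and counts five hospitals.

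Under Statistical methods {20a}, "A log-rank test will be used to compare Kaplan-Meier curves for the primary endpoint", and "All statistical tests will be performed using two-sided tests at the significance level 0.05". No strata are mentioned. Adjusted Cox models are optional and are meant for confounders that randomisation has left imbalanced, to be set against an unadjusted Cox model. The section on concomitant care {11d} also promises adjustment, but for concomitant treatment.

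Under Sample size {14}, the calculation takes "hazard ratio (HR) = 1.75" and 80% power, and adds: "we assume an overall probability of 80% for reaching the primary endpoint (clinical improvement) within 28 days". The formula has no centre term. The total follows: "Estimating a drop-out rate of 3% and considering block randomization, we aim to include 132 patients into the study".

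Section {20a} leaves the detailed methods to a separate SAP, which is not shown.

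**The concern.** The design treats centre as prognostic and the stated analysis then leaves it out. The adjustment clause cannot repair this, because centre is balanced by construction and so is not one of the imbalanced factors the clause covers.

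Two effects follow if centres differ. First, stratified allocation removes chance imbalance between arms in centre mix, so the log-rank numerator varies less than it would under simple randomisation. The ordinary log-rank variance does not credit this, and the test becomes conservative. Second, pooling centres with different underlying hazards pulls the overall hazard ratio towards 1.

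A centre effect is plausible from the article itself. There are five hospitals in three countries, each with its own written guidelines {6b}. The eligibility criteria {10} exclude high-flow oxygen, CPAP, ventilation and intensive care, so patients enter at level 3 or 4 of the WHO scale in Table 1. A fall of two levels from there means an ambulatory level, so the event is in effect live discharge, which can reflect local practice as well as recovery. At stake is the power of a trial that was sized with almost no reserve.

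**Working it through.** **1. Reproduce the planned size.** Inputs from {14}: two-sided alpha 0.05, power 80%, HR 1.75, event probability d = 0.8, 1:1 allocation.

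n = (z_alpha/2 + z_beta)² / (log(HR)² × 0.25 × d)

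- With the article's rounded z values: (1.96 + 0.84)² / (log(1.75)² × 0.25 × 0.8) = 125.17, matching the stated 125.2. Exact z values give 125.31.
- Drop-out: 126 / (1 − 0.03) = 129.9, so 130. Rounded up to a multiple of four, this is 132, as stated.
- Expected events: 132 × 0.97 × 0.8 = 102.4, which gives 80.8% power by the same formula.

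The planned figure is therefore right on its own terms, with under one point to spare.

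**2. Add a centre effect.** The article gives neither between-centre variation nor centre sizes, so both are assumptions. The main simulation used 128 analysed patients (132 less 3%), five centres, permuted blocks of four within centre, exponential times in whole days, censoring at day 28, overall event probability held at 0.80, and HR 1.75 applied within each centre. Both tests were run on the same data, with 8,000 trials per setting:

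- unstratified: Z = Σ(d1 − d × n1/n) / √ΣV, summed over event days with all centres pooled;
- stratified: the same sums formed within each centre, then added over centres.

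Results with near-equal centres (28/26/26/24/24):

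| SD of centre log-hazard | Power, unstratified | Power, stratified | Alpha, unstratified | Alpha, stratified |
|---|---|---|---|---|
| 0 | 80.0% | 78.5% | 0.051 | 0.053 |
| 0.25 | 78.5% | 78.5% | 0.045 | 0.052 |
| 0.5 | 70.8% | 78.7% | 0.033 | 0.052 |
| 0.75 | 59.1% | 78.0% | 0.020 | 0.053 |
| 1.0 | 44.9% | 77.7% | 0.012 | 0.055 |

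Results with unequal centres (60/32/16/12/8):

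| SD of centre log-hazard | Power, unstratified | Power, stratified | Alpha, unstratified | Alpha, stratified |
|---|---|---|---|---|
| 0 | 82.1% | 80.5% | 0.051 | 0.052 |
| 0.25 | 79.7% | 80.2% | 0.045 | 0.048 |
| 0.5 | 72.0% | 78.9% | 0.038 | 0.051 |
| 0.75 | 63.0% | 78.7% | 0.025 | 0.052 |
| 1.0 | 51.5% | 77.9% | 0.015 | 0.054 |

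Monte Carlo standard error is about 0.5 points for power and 0.0025 for alpha. As a guide to scale, SD 0.25 means about a 2-fold hazard ratio between the two extreme centres, and SD 0.5 about a 4-fold ratio.

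**3. Check against other set-ups** (power, unstratified against stratified).

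| Set-up | SD 0 | SD 0.3 | SD 0.5 | SD 0.7 |
|---|---|---|---|---|
| 132 patients, centres 48/36/24/14/10, 1,800 trials | 82 vs 81% | 79 vs 80% | 73 vs 78% | 67 vs 77% |
| 128 patients, 1,500 trials | 81 vs 80% | 78 vs 78% | 75 vs 79% | 67 vs 79% |

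Monte Carlo standard error is about 1 point here. In both set-ups, unstratified type I error falls to about 3%.

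**4. Read off the loss against the stratified test.** At SD 0.25 to 0.3 it is 0 to 1 point. At SD 0.5 it is 79 − 75 = 4, 78 − 73 = 5, 78.9 − 72.0 = 6.9 and 78.7 − 70.8 = 7.9 points. At SD 0.7 it is 77 − 67 = 10 and 79 − 67 = 12 points. At SD 0 the sign reverses: stratifying costs 1 to 1.6 points.

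**The case against.** The strongest objection is that the absence of strata is read from silence. The article does not call the test unstratified, and an article may leave strata to the SAP. The mention of an unadjusted Cox model does not settle it either, because there it is only the comparator for the optional adjusted models. This stands as a limit: a reader might infer that the SAP's test ignores centre, and the article does not show that. But the article does fix the primary test and a rule for adjustment, and that rule passes over the randomisation stratum. The wording needs settling whatever the SAP says.

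Second, the size is assumed. Nothing in the article says that discharge depends strongly on centre, and section {6b} lists elements of care used in the participating centres. This also stands, which is why a range is given. A reader might infer that 80% power holds only if all centres have equal rates. The simulations do not support that: at SD 0.25 to 0.3, unstratified power is still 78 to 80%.

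Third, stratifying does not fully restore 80% power. With near-equal centres and 3% drop-out, the stratified test stays at 77.7 to 78.7%. This is true; its merit is that it holds steady while the other test falls.

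Fourth, a reader might infer that the trial's validity is in doubt, or that the secondary analyses must change too. Neither follows. The unstratified test's type I error is at or below nominal, within simulation error, and no calculation was made for the secondary endpoints.

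**Conclusion.** The point holds as a mismatch between design and stated analysis that is cheap to remove. If centres differ, the log-rank test as stated is conservative and loses power. Against a centre-stratified test, the loss is negligible at an SD of the centre log-hazard of about 0.25 to 0.3, about 4 to 8 points at 0.5, and about 10 points or more at 0.7. If centres do not differ, the stated test is not conservative and is slightly the better of the two.

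This rests on the assumed SDs and centre sizes, on exponential times, on HR 1.75 applying within centre, and on reading the stated test as carrying no strata. It concerns efficiency and does not raise the risk of a false positive.

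**What to change.** Before database closure, specify the primary test as a log-rank test stratified by study centre, with the hazard ratio and 95% CI from a Cox model stratified by centre. Align the article and SAP wording; if the SAP already says this, only the article's description needs correcting. The article says that recruitment is ongoing, that analysts are blinded, and that the SAP is finalised before database closure, so the change can be made prospectively.

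The cost is a line of text and about 1 to 1.5 points of power if centres prove identical. Adjusting secondary endpoints for centre is optional.

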### Eligibility criteria {10}

Hospitalized patients with diagnosed COVID-19 are asked to take part in this study when the following eligibility criteria are fulfilled:▪ SARS-CoV-2 infection, verified according to current in-house guidelines▪ High risk for the development of ARDS:i.e., within 24 h before inclusion at least 2 points on an adapted EALI (early acute lung injury) score, with at least one point from the original EALI score [52, 53]Original EALI score:◦ 2–6 l O_2_ supplementation to achieve a SaO_2_ > 90%: 1 point◦ > 6 l O_2_ supplementation to achieve a SaO_2_ > 90%: 2 points◦ Respiratory rate ≥ 30/min: 1 point◦ Immunosuppression: 1 pointModification adapting for risk factors for ARDS in COVID-19 affected patients [54]◦ Arterial hypertension: 1 point◦ Diabetes: 1 point◦ Fever > 39 °C: 1 point▪ Age ≥ 18 years▪ Ability to comply with the inhalation maneuver▪ Ability to understand the clinical trial and sign the informed consent

The presence of any of the following exclusion criteria will lead to exclusion of the patient:▪ Mechanical ventilation or intensive care treatment within current hospitalization▪ Nasal high-flow cannula or continuous positive airway pressure (cPAP) ventilation at time of inclusion▪ Inability to conduct inhalation therapy▪ Hemodynamic instability with requirement of vasopressor therapy▪ Severe comorbidities interfering with the safe participation according to the treating physician▪ Previous participation in this trial, or current participation in another interventional study▪ Pregnancy▪ Systemic immunosuppression for chronic underlying condition (corticosteroid treatment as part of “standard care” allowed)

“Drop-out” is defined as the patient’s withdrawal of consent at any time after inclusion into the study.

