#### Relevant concomitant care permitted or prohibited during the trial {11d}

All treatments considered necessary by treating doctors are permitted and their use is recorded in the case report form. Because inhaled aviptadil does not reach the systemic circulation and is mainly metabolized in the lung, pharmacokinetic interactions with aviptadil are not expected. In order to account for potential bias, we aim to analyze data from patients, who received potentially biasing concomitant treatment (e.g., immunosuppressants or immunomodulators) in an adjusted manner (see Statistical methods for primary and secondary outcomes {20a}).

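### Covariates for the adjusted primary-outcome Cox model are picked by observed imbalance and the model is optional; one prespecified severity-adjusted model would gain precision and close the choice

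*Protocol article*

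**What the plan says.** Under Statistical methods for primary and secondary outcomes {20a}, the primary comparison is unadjusted: "A log-rank test will be used to compare Kaplan-Meier curves for the primary endpoint". The rule for adjustment follows: "For potential confounders that are not fully balanced by randomization, adjusted analyses for the primary outcome may be performed using Cox regression models", with the result set out "to compare with the respective unadjusted Cox model". No covariate is named, no criterion for imbalance is given, and the wording makes the analysis optional.

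The section on concomitant care {11d} adds a second intention, "we aim to analyze data from patients, who received potentially biasing concomitant treatment", in an adjusted manner, and refers back to {20a}. Section {11b} lets concomitant medication change at any time, so this is not a set of baseline covariates.

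Severity is known at entry. Every patient must have "within 24 h before inclusion at least 2 points on an adapted EALI (early acute lung injury) score" (Eligibility criteria {10}), which requires oxygen flow and respiratory rate. The first footnote to Fig. 1 lists "demographics, clinical status according to nine-level ordinal scale, medical history, smoking status, COVID-19 symptoms, and COVID-19 vaccination status". Severity is not a randomization factor: "Randomization is stratified by study center in order to account for differences in standard of care" (Sequence generation {16a}).

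**The concern.** Precision from covariate adjustment comes from how strongly a baseline variable predicts the outcome. It does not depend on whether the arms happen to differ on that variable. A rule that waits for imbalance leaves out a strong predictor in most randomizations and may bring in a weak one in others.

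The rule is also applied after the data are seen, with neither the variables nor the threshold stated. An adjusted hazard ratio may then appear or not appear beside the unadjusted one, with a covariate set chosen late. At stake are the precision of the treatment effect in a trial of 132 patients and the credibility of the supportive estimate.

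**Working it through.** **The plan's own figure.** Inputs from Sample size {14}: HR 1.75, two-sided alpha 0.05, power 80%, 80% of patients improving by day 28, 1:1 allocation, 3% drop-out.

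- n = (1.96 + 0.84)² / (ln(1.75)² × 0.25 × 0.8) = 7.84 / (0.3132 × 0.2) = 125.2, as stated.
- 125.2 / 0.97 = 129.1, so 130; the next multiple of the block size 4 is 132, as stated.
- Events at n = 132: 132 × 0.8 = 105.6. Power = Φ(√(105.6/4) × 0.5596 − 1.96) = Φ(0.915) = 82%. At 128 evaluable patients (132 × 0.97) it is 81%.

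The sample size is correct for an unadjusted test of a hazard ratio of 1.75.

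**What the adjustment rule does.** Simulation: n = 132, exponential times, censoring at day 28, baseline hazard set so that 80% have an event overall, and one standard-normal baseline severity score (4,000 runs per cell; Monte Carlo SE at most 0.8 points). Three analyses are compared: the log-rank test; Cox adjusted only if the score differs between arms at p < 0.10; and Cox always adjusted. The score's strength and the p < 0.10 threshold are assumptions, because the protocol gives neither.

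Power (%), HR 1.75 read as **conditional** on the score:

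| log-HR per SD | marginal HR implied | log-rank | adjust if imbalanced | always adjust |
|---|---|---|---|---|
| 0.3 | 1.71 | 77.7 | 78.1 | 81.5 |
| 0.5 | 1.64 | 70.6 | 72.2 | 80.3 |
| 0.7 | 1.57 | 61.7 | 64.0 | 80.5 |

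A separate run of this design gave 79/73/62, 80/74/64 and 82/82/81.

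Power (%), HR 1.75 read as **marginal**:

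| log-HR per SD | conditional HR implied | log-rank | adjust if imbalanced | always adjust |
|---|---|---|---|---|
| 0.3 | 1.80 | 81.8 | 82.1 | 85.3 |
| 0.5 | 1.89 | 82.3 | 83.4 | 90.0 |
| 0.7 | 2.01 | 81.4 | 83.4 | 94.1 |

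**A binary severity factor instead** (128 evaluable patients, 4,000 runs), log-rank against always adjusted:

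- Conditional 1.75, 50:50 split: 79 v 81% (factor HR 1.5), 75 v 81% (2.0), 66 v 80% (3.0).
- Conditional 1.75, 10:90 split: 80 v 80%, 79 v 81%, 77 v 82% for the same three strengths.
- Roughly marginal 1.75 (realized 1.77–1.80), 50:50 split: 82 v 84% (1.5), 83 v 87% (2.0), 84 v 91% (2.5), 84 v 94% (3.0).

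In every setting the imbalance trigger adds at most about 2 points to the log-rank, even if its result decided the trial. At p < 0.10 it fires for a given covariate in only about one randomization in ten.

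**Type I error.** Each single fixed analysis runs at about 5%; the p < 0.10 trigger gave 4.4–4.8%. Reporting whichever of the log-rank and one adjusted model is significant gives about 6–8%. With the covariate set left free (each factor HR 1.5) it is about 8% with three covariates and 10% with five.

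**The case against.** A reader might infer that the trial misses its planned 80% power. The documents do not support that. Sample size {14} states the hazard of one arm relative to the other without covariates, so 1.75 reads most naturally as marginal. The log-rank then has the power claimed, and adjustment is a gain on top, not the repair of a deficit.

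A reader might also infer that the trial's 5% error is at risk. It is not: the log-rank test is named as primary, and the inflated rates above need selective reporting, which the protocol does not propose. They show only what an open choice would allow.

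Three further points have weight.

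- The documents give no prognostic strength. A weak or very unevenly split covariate yields 0–2 points.
- Entry severity is narrower than it looks. The exclusion "Nasal high-flow cannula or continuous positive airway pressure (cPAP) ventilation at time of inclusion" leaves WHO level essentially at 3 or 4, and the required point from the original EALI score means that few patients can enter without oxygen. The Fig. 1 footnote lists neither oxygen flow nor the EALI score, although eligibility cannot be judged without them.
- Detailed methods are deferred to a SAP that is not shown and may name covariates. An unlisted covariate set is therefore not the point. The point is the selection rule that the protocol does print; if the SAP differs, the two need aligning.

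**Conclusion.** The concern stands as an inefficient and loosely fixed supportive analysis, not as a flaw in the primary test or the sample size. Selecting covariates by imbalance captures almost none of the available precision and leaves the adjusted hazard ratio open to data-driven choice.

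The size of the lost opportunity rests on two things that the documents do not settle: the strength of baseline severity as a predictor, and whether 1.75 is marginal or conditional. On the marginal reading, prespecified adjustment adds roughly 2 to 13 points to a log-rank that already meets its target. On the conditional reading, it restores about 80–82% where the log-rank would fall to between about 79% and 62%. The change is worth making because the information is gathered at entry and no extra patients are needed.

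**What to change.** Before unblinding:

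1. Delete the imbalance trigger and the optional wording in {20a}.
2. Prespecify one Cox model, stratified by center, with treatment, age, and baseline oxygen requirement or adapted EALI score. WHO level alone is not enough. With about 106 events, two or three covariates are safe.
3. Preferably make this model the primary test and estimate, with the log-rank as support. The power gain reaches the primary conclusion only this way.
4. Otherwise keep the log-rank as primary and make this model the single named supportive analysis, always reported beside it. This closes the choice of covariates but adds no primary power.
5. Keep treatment started after randomization out of the model, and align the statement in {11d} with this.

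Cost: no patients or assessments are added, but confirm that the entry oxygen flow or EALI score is held in the database. The hazard ratio becomes conditional on the covariates, which the report should say. Option 3 changes the stated primary method and needs a protocol amendment before unblinding; option 4 needs new wording in the protocol and SAP.
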